## Statistical Analysis Plan for the POST-Renal Study

This statistical analysis plan was finalized and agreed upon by the POST-RENAL Study Investigators on 7^th^ February 2012, with all statistical analysis of the locked study dataset occurring after this date.

### Study synopsis

| Study Title | Prolonged Outcomes Study of the RENAL Study (POST-RENAL) Study |
| --- | --- |
| Study Rationale | Acute Kidney Injury (AKI) is an increasingly common condition which is associated with high mortality. In survivors the outcomes are poorly understood with some registry studies suggesting that rates of subsequent kidney failure are high. There are no large scale prolonged follow up studies to define the longer term consequences of AKI. POST-RENAL will extend the follow up of the largest randomized trial in the field to describe these outcomes. |
| Study Design | Cohort study |
| Subject Participation | Single visit followed by single telephone survey |
| Rationale for Number of  Subjects | Survivors of randomized trial at approximately 3.5 years following randomization |
| Approximate Duration of Study | 18 months |
| Study Outcomes | Primary: Mortality  Secondary: Requirement for renal replacement therapy, Presence of markers of kidney disease and dysfunction, Quality of life. |
| Criteria for Inclusion | Survivors at 90 days following randomization in the RENAL Study |
| Criteria for Exclusion | Died within 90 days following randomization in the RENAL Study |
| Number of Subjects | 810 survivors at 90 days |
| Number of Study Centres | 35 Intensive Care Units that participated in the RENAL Study |
| Treatment Administration | Nil treatment administered |
| Safety Evaluation | As a cohort study with no interventions few safety issues are envisaged. Adverse events will be reported and monitored by the study Steering Committee. |
| Statistical Analysis, interim and final | There will be no interim analysis. The final analysis will compare the primary and secondary outcomes using log rank test, Students t test, Chi squared and the Mann-Whitney U test as appropriate. Odds ratios will be estimated using multivariate logistic regression analysis. |

### Background and rationale

The incidence of Acute Kidney Injury (AKI) is increasing with overall rates exceeding that of end-stage kidney disease by a factor of 15-fold[^1-3^](#_ENREF_1). In its most severe form, where patients require dialysis in an ICU, the mortality is over 50%[^3^](#_ENREF_3)^,^[^4^](#_ENREF_4). There are no treatments proven to reduce this mortality and there is little long term follow up data from large studies of survivors from an episode of severe AKI.

Beyond the mortality of AKI, the long term renal outcomes of survivors of AKI remain unclear. One small case series[^5^](#_ENREF_5) suggested relative preservation of renal function in survivors of AKI but there is very little data beyond hospital discharge. The VA/NIH trial reported very high rates of renal failure and dialysis dependence in the surviving patients, with 75% of survivors showing no recovery of renal function by day 28[^6^](#_ENREF_6). In addition a recent publication linking hospital admissions data with the US Renal Data System Registry [^7^](#_ENREF_7) suggests that patients with AKI had a 13 fold increase in the risk of developing end stage kidney disease over the following 2 years. This risk rose to 42 fold if the patient had chronic kidney disease in addition to an episode of AKI. These recent studies of large numbers of patients raise very serious concerns about the long term renal outcomes of AKI. However, the evidence is limited by the small numbers, short follow up and reliance upon admission coding data. There is no prolonged follow up assessment of a large cohort of patients with AKI from a randomized controlled multi-centre study.

The RENAL Study, an NHMRC funded multi-centre RCT, is the largest study of AKI treatment and randomized 1508 patients to two different dialysis dose intensities in 35 centres across Australia and New Zealand. It completed follow up on 97.1% of randomized patients out to 90 days[^8^](#_ENREF_8). There were no differences in patient mortality between the normal and augmented intensity dialysis groups and the mortality in both groups was 45%. The large numbers of patients enrolled in the RENAL Study, the demonstrated completeness of data and the absence of such follow up from the literature represent an unprecedented opportunity to define the long term outcomes of AKI in a unique manner.

This study will extend the follow up of survivors from the RENAL Study to a median of 3.5 years to provide high quality evidence regarding the long term consequences of an episode of severe AKI which represents a serious gap in our knowledge. The follow up will focus upon the mortality rates along with the frequency of markers for future renal and cardiovascular disease such as blood pressure, renal function, urinary abnormalities and quality of life.

### Study objectives

Primary Objective

The primary objective of the POST-RENAL Study is to compare long-term overall survival of adult patients with acute renal failure according to treatment allocation in the RENAL study.

Secondary Objectives

The secondary outcomes will include:

1. Dialysis free days (for all patients at the start of RENAL study, for patients alive at Day 28, for patients alive at Day 60 and patients alive at Day 90)
2. Time to first return to dialysis beyond Day 90 (death censored)
3. Causes of death, competing risk of dialysis/Death
4. Blood pressure and requirement for treatment for high blood pressure
5. Renal function: as measured by serum creatinine and eGFR
6. Proteinuria, as measured by urine albumin:creatinine ratio
7. Quality of life: as measured by two measures (EQ-5D and SF-12)

In this study, adverse events are likely to be extremely rare due to lack of a study intervention beyond data collection. However it is possible for adverse events to arise from the interactions required for participation in the study (eg. resulting from procedure of blood collection) and these will be reportable to the coordinating centre and local ethics committee where applicable.

1. Number of events and number and proportion of patients experienced serious adverse events

### Study design

This study is a cohort study, deriving extended follow up of all survivors of an earlier randomized controlled trial (the RENAL Study). The outcomes of the RENAL Study at 90 days post randomization has been ascertained on 97.1% of participants with 55% of these patients surviving.

### Study population

The study population is that of all patients alive at 90 days following randomization in the RENAL study (the primary outcome of that study). Accordingly, the POST-RENAL study will seek to operate in the same centres. The RENAL Study randomized 1508 patients in 35 centres in Australia and New Zealand.

The outcomes of the RENAL Study at 90 days post randomization has been ascertained on 97.1% (n=1464) of participants with 55% (n = 810) of these patients surviving. The first patient was enrolled in the study in December 2005 and the last in August 2008. We will follow up all patients alive at 90 days following randomization at median 3.5 years (+/- 6 months) post randomization.

Follow up will be sought on all survivors from July 2010. Where the patient has died beyond the 90 day follow up of the study, limited data on important events (requirement for dialysis, date of death, cause of death) will be sought. Those who are still alive at the time of extended follow up will be asked to consent to the full data collection.

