   3. GIT
   4. Neurological
   5. Sepsis
   6. Trauma without traumatic brain injury
   7. Traumatic brain injury +/- multiple trauma
   8. Metabolic
   9. Haematological
   10. Burns
   11. Renal
   12. Other medical
9. Severe sepsis at baseline
10. APACHE III score
11. SOFA score
    1. Cardiovascular domain
    2. Respiratory domain
    3. Hepatic domain
    4. Haematologic domain

(SOFA score domains will be analyzed as continuous variables and as categorical variables divided into normal function (SOFA score 0) dysfunction (SOFA score 1-2) and failure: SOFA score 3-4).

1. Last serum urea concentration before randomization
2. Last serum creatinine concentration before randomization
3. Haematological variables
4. Biochemical variables
5. Treatment with mechanical ventilation
6. Estimated glomerular filtration rate (eGFR)
7. Presence of an estimated glomerular filtration rate (eGFR) <60 ml/min

The eGFR will be calculated using the revised modification of diet in renal disease (MDRD) equation[^9^](#_ENREF_9):

eGFR = 175 × (SCr x 0.0113)^-1.154^ × (age)^-0.203^ ×((0.742 [if female]))

SCr is serum creatinine level in micromol/L

Primary analysis

The primary outcome of mortality will be reported as a survival analysis from the time patients are randomized into the RENAL study. Survival curves and estimated median survival time and its 95% confidence interval will be generated according to the Kaplan-Meier method. Data will be censored at the time when the patient was last known to be alive or to be discharged from hospital. Log-rank test will be used to assess the difference between the two survival curves.

Multivariate Cox model will be performed to provide an adjusted long term survival curve of survivors of acute kidney injury. To determine which variables to include in the multivariate Cox model, we will run first a univariate Cox regression on each baseline variable and select variables with a p-value <= 0.01.

The number of events and the median survival (if available including 95% CI) will also be reported.

Secondary analysis

Time-to-event (Time to first return to dialysis beyond Day 90, Time-to-specific cause of death) will be analysed using the same principles as in the primary outcome. Because the two events Death and First return to dialysis are competing events, data will be censored at the time of competing event if it occurs first. Log-rank test will be used to assess the difference between the two survival curves.

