### Tables and Figures

Table 1 : Baseline characteristic (to RENAL study patients to POST-RENAL study patients)

Table 2: Time-to-event outcomes

Table 3: Binary and continuous outcomes

Figure 1 : Kaplan Meier graph of survival time from original randomization in the RENAL

Figure 2 : Kaplan Meier graph of Time to first return to dialysis beyond Day 90 (stratified by the original randomization)

Figure 3 : Kaplan Meier graph of Time to Death for Day 90 survivors

Figure 4 : Estimates of probabilities of Death and first return-to-Dialysis based on cumulative incidence functions

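### The stated population (810 Day-90 survivors) does not fit the primary objective or the time origin at randomisation, and no sentence names the set for the primary log-rank test

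*SAP*

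**What the plan says.** Three parts of the SAP restrict the study to Day-90 survivors.

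- **Study population:** "The study population is that of all patients alive at 90 days following randomization in the RENAL study".
- **Study synopsis:** the exclusion criterion is "Died within 90 days following randomization in the RENAL Study" and the number of subjects is "810 survivors at 90 days".
- **Study design:** the study is described as extended follow-up of the RENAL survivors.

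Two parts point to everyone randomised.

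- **Study objectives:** the primary objective is to "compare long-term overall survival of adult patients with acute renal failure according to treatment allocation in the RENAL study". It carries no Day-90 condition.
- **Statistical analysis, Primary analysis:** "The primary outcome of mortality will be reported as a survival analysis from the time patients are randomized into the RENAL study". A log-rank test then compares the two curves. No analysis set is named.

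The remaining text does not settle the matter. The General principles have all outcomes analysed both by original allocation and as one cohort, without saying which patients are counted. The Cox model in the Primary analysis section is aimed at survivors of acute kidney injury. Under Tables and Figures, Figure 1 shows survival from original randomisation with no set named, and Figure 3 is a "Kaplan Meier graph of Time to Death for Day 90 survivors" with no time origin given.

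**The concern.** A stated exclusion rule conflicts with the stated objective and time origin of the only primary test. An analyst who applies the exclusion and then times survival from randomisation gets a hybrid: 810 patients, none of whom can die in the first 90 days, with every earlier death left out. An analyst who follows the objective uses all 1508 patients.

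These are different questions. The all-randomised analysis keeps the randomised comparison. The survivor analysis conditions on Day-90 survival, which the SAP itself identifies as the primary outcome of RENAL and which the allocated treatment could in principle affect. The two also differ widely in number of deaths, survival level and whether a median can be estimated. The Day-90 results were already known when the SAP was agreed, so the set should be fixed in writing.

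**Working it through.** **1. The SAP's own counts** (Study population section)

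- Day-90 status known: 1464/1508 = 97.1%, as stated.
- Alive at Day 90: 810/1464 = 55.3%, agreeing with the stated 55%.
- Dead by Day 90: 1464 − 810 = 654, or 44.7%, agreeing with the stated 45% mortality.
- Day-90 status unknown: 1508 − 1464 = 44.

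The counts are consistent with one another. The problem lies in which of them enter the primary analysis.

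**2. Deaths and survival under each set**

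The SAP gives no mortality after Day 90. Assume that a proportion p = 20% to 40% of the 810 die by 3.5 years. The 44 with unknown status are left out of this arithmetic.

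| | All randomised, from randomisation | Day-90 survivors only |
|---|---|---|
| Deaths, p = 20% | 654 + 162 = 816 | 810 × 0.20 = 162 |
| Deaths, p = 40% | 654 + 324 = 978 | 810 × 0.40 = 324 |
| Alive at 3.5 years, p = 20% | 648/1464 = 44% | 80% |
| Alive at 3.5 years, p = 40% | 486/1464 = 33% | 60% |

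The early deaths are 654/816 = 80% to 654/978 = 67% of all deaths, and they enter only one version. Since 3.5 years is a median follow-up, these are deaths projected to 3.5 years and not the exact counts the analysis would observe.

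**3. Detectable effect**

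With D deaths, equal arms, two-sided 5% and 80% power, the detectable hazard ratio is exp(−2 × (1.960 + 0.842)/√D).

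- All randomised: 0.82 (D = 816) to 0.84 (D = 978).
- Survivors only: 0.64 (D = 162) to 0.73 (D = 324).

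**4. Median survival**, which the Primary analysis section asks for where available

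With all randomised patients, the curve stands at 0.553 at Day 90 and reaches 0.5 once 1 − 0.5/0.553 = 9.6% of the survivors have died. Among the 810 alone, survival at 3.5 years is 60–80% over the assumed range, so the median is not reached by then.

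**5. What the 90 event-free days do**

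In the hybrid they add 810 × 90/365.25 = 200 person-years in which no death can occur. The curve is flat at 100% to Day 90, and any median is 90 days longer than one measured from Day 90. In simulated data with p = 20%, 30% and 40% and an assumed follow-up uniform over 1.9 to 4.6 years, the crude death rate came out 8–9% too low.

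The log-rank test does not change. All 810 are known to be alive at Day 90, so nobody dies or leaves the risk set before then, and moving the origin by 90 days leaves the order of events and every risk set as they were. In the same three datasets the log-rank Z was identical with either origin (0.47, −2.68 and 0.68).

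**6. What conditioning on survival does**

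In an illustrative frailty model (assumed; 150 replicates per setting) with no direct treatment effect after Day 90, the rate ratio among survivors averaged 1.02 with no early effect, 1.10 with an early hazard ratio of 0.8, and 1.13 with 0.7. The mechanism is real, but it needs an early effect, and the 45% mortality reported for both groups gives no sign of one.

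**The case against.** The strongest reply is that the documents point to one sensible reading. The objective has no Day-90 condition, the clock starts at randomisation, and of Figures 1 and 3 only Figure 3 is labelled as survivors. Under the hybrid the two figures would show the same 810 patients and the same deaths, shifted by at most 90 days, which is unlikely to be what was meant. The Study population section can be read as describing whom to trace and ask for consent, because earlier deaths are already recorded in RENAL. The censoring rule at last known alive already covers the 44 with unknown status.

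Much of this stands. It supports an inference about intent, but it does not supply the missing sentence, and it leaves an exclusion criterion that says the opposite. The authors do name sets where they choose to: dialysis-free days are specified for all patients and for those alive at Days 28, 60 and 90.

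A reader might infer three stronger things that the documents do not support.

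- **That immortal time biases the comparison between arms.** It does not. The 90 days are the same in both arms and the log-rank is unchanged. Only absolute quantities shift.
- **That the flawed hybrid was planned.** The figure list suggests otherwise.
- **That the synopsis row "Survivors of randomized trial at approximately 3.5 years following randomization" defines a third analysis set.** It stands under the rationale for the number of subjects and is best read as loose wording about when follow-up takes place.

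**Conclusion.** The point holds as an unresolved conflict. The stated population and exclusion do not fit the primary objective and time origin, and the set for the primary log-rank test is not named. If the exclusion were applied to the primary analysis, 654 deaths would be omitted, the comparison by arm would be conditional on Day-90 survival, and the Kaplan-Meier level and any median would be inflated by 90 event-free days. The loss of randomised protection is a matter of principle here; with 45% mortality in both groups, the actual imbalance may be small.

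The 654, 810, 1464 and 44 come from the SAP or follow from it by subtraction. The contrast of 816–978 with 162–324 deaths, and the survival and detectable-effect figures built on it, rest on the assumed 20–40% later mortality. The conflict itself does not depend on that assumption.

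**What to change.** Three wording changes:

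1. **Primary analysis section.** State that the primary analysis compares the allocated groups in all 1508 randomised patients, timed from randomisation and shown in Figure 1, with patients of unknown Day-90 status censored when last known alive.
2. **The same section and the figure list.** State that the 810 Day-90 survivors form a secondary landmark analysis with time zero at Day 90, shown in Figure 3 and interpreted as conditional on survival to Day 90. Say which set the Cox model uses.
3. **Synopsis and Study population section.** Describe the 810 as the cohort for extended follow-up and data collection, so that the exclusion no longer reads as a rule for the primary analysis.

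The cost is SAP wording only. Day-90 outcomes are already ascertained for 1464 patients, and the SAP already draws on the RENAL database, so no new data collection should be needed.

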### Statistical analysis

General principles

1. There are no treatments associated with POST-RENAL, as it constitutes an extended follow up of survivors from a previous randomized trial. However all primary and secondary outcomes will be analysed as according to original randomization in the RENAL Study as well as a cohort.
2. All tests are two-sided and the nominal level of alpha will be 5%.
3. All statistical analyses will be unadjusted except where indicated.
4. Subgroup analyses will be carried out irrespective of whether there is a significant effect of treatment on the primary outcome.
5. We will not impute missing values unless specified otherwise. We will report the number of observations used in the analysis.
6. P-values will not be adjusted for multiplicity. However the outcomes are clearly categorized by degree of importance (primary, secondary and tertiary) and a limited number of subgroup analyses are pre-specified.

Baseline characteristics of patients

Description of the following baseline characteristics will be presented by treatment group. Data for Day 90 survivors will be extracted from RENAL study database. Discrete variables will be summarized by frequencies and percentages. Percentages will be calculated according to the number of patients for whom data are available. Where values are missing, the denominator (which will be less than the number of patients assigned to the treatment group) will be stated in either the body or a footnote in the corresponding summary table. In some instances, additional frequencies and percentages of patients in each category will be reported as indicated in the list below. Continuous variables will be summarized by use of standard measures of central tendency and dispersion using mean and standard deviation as well as quantile points at 0.25, 0.5 and 0.75 where appropriate.

1. Sex
2. Age
3. Weight
4. Percentage of patients with measured weight, percentage of patients with estimated weight and method of weight estimation.
5. Source of admission to ICU (emergency department, hospital floor, another ICU, another hospital, operating room (OR) following emergency surgery, OR following elective surgery, readmission to the same ICU during same hospitalization)
6. Operative or non-operative admission
7. Operative admission diagnosis (number and % in categories a-k)
   1. Cardiovascular
   2. Respiratory

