As this cause-specific analysis can potentially be biased due to the presence of different cause of death, a competing risk analysis will also be undertaken if the number of competing events (Death and return to dialysis) occurring is moderate to large (e.g. > 10%). This could typically be based on the CIF and the Gray’s test.

For binary secondary outcomes (i.e. Requirement for treatment for high blood pressure), a standard Chi-square test will be used to assess the effect of treatment. Frequencies and percentages per arm, possibly a relative risk (or odds-ratio) measuring the treatment effect and its 95% CI will also be reported along with the p-value of the chi-squared test.

Continuous secondary outcomes (i.e. time to free requirement for dialysis, Blood pressure, Renal function: as measured by serum creatinine and eGFR and Proteinuria, as measured by urine albumin:creatinine ratio) will be summarized by use of mean and standard deviation as well as quantile points at 0.25, 0.5 and 0.75 reported. Comparison in differences in mean between the two groups will be carried out using univariate/multivariate linear regression.

Quality of life: as measured by two measures (EQ-5D and SF-12)

Descriptive statistics of individual responses to the 5 EQ-5D questions and to the 12 SF-12 questions by treatment allocation will be provided. Statistics will include the difference in mean score between the two group.

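### Blood pressure, renal function, albumin:creatinine ratio and quality of life are observed only in living, consenting survivors, and the SAP reports them as cohort results without any step for non-participation

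*SAP*

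**What the plan says.** **Population and timing (Study population).** "The study population is that of all patients alive at 90 days following randomization in the RENAL study". The section gives Day-90 outcome as known for "97.1% (n=1464) of participants with 55% (n = 810) of these patients surviving", and the timing as: "We will follow up all patients alive at 90 days following randomization at median 3.5 years (+/- 6 months) post randomization".

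**Who supplies which data (same section).** For patients who died after Day 90, only dialysis requirement, date of death and cause of death are sought. For the living: "Those who are still alive at the time of extended follow up will be asked to consent to the full data collection". Secondary outcomes 4 to 7 under Study objectives (blood pressure and its treatment, renal function, proteinuria, EQ-5D and SF-12) therefore rest on the consenting living.

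**What the results are for (Background and rationale).** "The follow up will focus upon the mortality rates along with the frequency of markers for future renal and cardiovascular disease", with blood pressure, renal function, urinary abnormalities and quality of life as the examples. General principles, item 1, has every primary and secondary outcome analysed by randomised arm and also as a cohort.

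**How missing data are handled (General principles, items 3 and 5).** Analyses are unadjusted unless indicated. "We will not impute missing values unless specified otherwise", and the number of observations used will be reported. No exception is given for the marker or quality-of-life outcomes.

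**How arms are compared (Secondary analysis).** For binary outcomes, with requirement for blood-pressure treatment as the one named, "a standard Chi-square test will be used to assess the effect of treatment". Continuous markers are summarised by means and quantiles and compared by univariate or multivariate linear regression. Quality of life is described by arm with a difference in mean score.

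**Tables and Figures.** Table 1 sets RENAL patients beside POST-RENAL patients at baseline.

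**The concern.** The plan names one population, all Day-90 survivors, and observes these outcomes in another: those who lived to the visit and then agreed to it. Two separate steps lie between them.

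- **Death before the visit.** A creatinine or EQ-5D value after death is undefined, not missing. This is a question of which population the estimate is for, and the SAP does not settle it.
- **Non-participation among the living.** These values exist but are not observed. If willingness to attend, give samples or answer a survey is related to kidney function or health, a complete-case mean or proportion is biased for living survivors.

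The SAP plans no weighting, bounds, sensitivity analysis or explicit comparison of participants with living non-participants. A reader could take a figure for volunteers as the long-term state of survivors of severe AKI, with a confidence interval that reflects sampling error alone.

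The arm comparison has a related weakness. Membership of the analysed group depends on surviving and consenting, both of which follow randomisation, so randomisation does not by itself protect a comparison within that group. For requirement for blood-pressure treatment, the SAP nevertheless describes the comparison in treatment-effect language.

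**Working it through.** **1. The denominators.** Using 1508 randomised, 1464 with known outcome and 810 survivors (Study population):

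- 1464/1508 = 97.08%, which agrees with the stated 97.1%.
- 810/1464 = 55.33%, which agrees with the stated 55%.

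The target of 810 is consistent. The SAP states no participation rate, late mortality, marker prevalence or target precision, so everything below is illustrative and uses assumed inputs. A binary marker is used only for simplicity. The SAP analyses the albumin:creatinine ratio, eGFR and blood pressure as continuous, and the same reasoning applies to a mean.

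**2. How many patients might contribute.** Assume 20-40% of the 810 die before the visit and 50-90% of the living consent.

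- Fewest: 810 × 0.60 × 0.50 = 243, or 30% of 810.
- Most: 810 × 0.80 × 0.90 = 583, or 72% of 810.

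**3. Error if non-participants differ.** With participation *c*, prevalence 35% in participants and *q* in living non-participants:

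true prevalence = 0.35*c* + *q*(1 − *c*), so error = (1 − *c*)(*q* − 0.35).

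Sampling half-width = 1.96 × √(0.35 × 0.65/*n*), with *n* = 810 × 0.70 × *c* (30% late deaths assumed).

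| *c* | *n* | True, *q* = 45% | True, *q* = 55% | Error, points | Half-width, points |
|---|---|---|---|---|---|
| 60% | 340 | 39% | 43% | 4 to 8 | 5.1 |
| 80% | 454 | 37% | 39% | 2 to 4 | 4.4 |

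At 60% participation the error is of the same order as the sampling uncertainty. At 80% it is smaller.

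**4. The sign is not fixed.** Step 3 assumes that non-participants are worse off. Now let consent depend on marker status, with a true prevalence of 40%:

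observed = 0.40*c*₁/(0.40*c*₁ + 0.60*c*₀), where *c*₁ and *c*₀ are the consent rates with and without the marker.

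- *c*₁ = 50%, *c*₀ = 70%: 0.20/(0.20 + 0.42) = 32.3%, too low.
- *c*₁ = 70%, *c*₀ = 50%: 0.28/(0.28 + 0.30) = 48.3%, too high.

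**5. Worst-case bounds among the living.** If 40% of participants have the marker, the bounds are 0.40*c* to 0.40*c* + (1 − *c*). Half-widths again assume 30% late deaths.

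| *c* | *n* | Bounds | Width, points | Sampling half-width, points |
|---|---|---|---|---|
| 50% | 284 | 20% to 70% | 50 | 5.7 |
| 70% | 397 | 28% to 58% | 30 | 4.8 |
| 90% | 510 | 36% to 46% | 10 | 4.3 |

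These extremes are not forecasts. They show what the data alone can exclude. Even at 90% consent, the 10-point range is slightly wider than the full sampling interval of 2 × 4.3 = 8.6 points.

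**The case against.** **The plan is open about who supplies data.** Consent from living patients cannot be avoided. The SAP says who gives full data, commits to reporting the number of observations and plans a baseline table. Complete-case analysis with disclosed denominators is a recognised choice. This stands as far as disclosure goes. It does not supply a correction or a bound. Nor need Table 1 reveal the selection: on the SAP's own definition the POST-RENAL patients are all 810, so consenters need not be separated from living non-consenters. Multivariate regression is offered for differences between arms, and does not repair a cohort mean or proportion.

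**The direction is unknown.** A reader might infer that the results must be optimistic because the frailest survivors stay away. The document does not support this. Patients with known kidney disease may be easier to reach, and step 4 shows the sign then reverses.

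**The arm comparisons are mostly worded descriptively.** A reader might infer that all of them are presented as causal. They are not. The treatment-effect wording belongs to binary secondary outcomes, of which requirement for blood-pressure treatment is the only one named. Continuous markers and quality of life are described as differences between groups. The Background also reports no mortality difference between the RENAL arms, at 45% in both, which makes strong differential selection by Day 90 less likely. It does not show that later survival and consent are balanced.

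**Weighting is an imperfect remedy.** Variables recorded in the ICU cannot capture frailty that develops afterwards. The SAP expects some missing baseline values, and Day-90 dialysis status is not in its baseline list. Survival is censored when a patient was last known alive, so vital status may be unknown for untraced patients. All of this stands, and it limits weighting to a sensitivity analysis among those known to be alive.

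**Conclusion.** The point holds as a cheap improvement to the secondary analyses. The SAP defines its population as all Day-90 survivors. It observes the marker and quality-of-life outcomes only in living consenters, analyses them complete-case and unadjusted, and takes no step to correct for non-participation.

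Neither the direction nor the size of the bias can be determined from the document. The illustrations rest on assumed participation, late mortality and prevalence, and at 80% participation the error is below the sampling half-width. A reader might infer that the bias matches a precision the trial promised, but the SAP states none.

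Nor should this be read as a fault in the primary outcome. Mortality does not depend on consent to the full data collection in the same way.

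**What to change.** 1. **Target.** Under Secondary analysis, state that results for blood pressure, requirement for blood-pressure treatment, renal function, albumin:creatinine ratio and quality of life refer to patients alive at extended follow-up.
2. **Sensitivity analysis.** Keep the complete-case result. Pre-specify, for the cohort estimates, an analysis that weights participants by the inverse of their estimated probability of taking part among those known alive. Use RENAL baseline variables (age, sex, APACHE III, severe sepsis, ventilation) and arm, plus Day-90 dialysis status where held. Say how missing predictors are handled.
3. **Table 1.** Show participants beside living non-participants.
4. **Wording.** For requirement for blood-pressure treatment only, replace both treatment-effect phrases under Secondary analysis with: difference between arms among participating survivors. Label the other marker and quality-of-life comparisons as being among participating survivors.

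**Cost.** SAP text, one table split and one supplementary analysis on data largely already held. Weighted intervals will be wider. Selection through later, unmeasured frailty will remain, and the report should say so.
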